#### Data management

Data will be stored securely at the study location. Data will be collected in REDCap electronic data capture tools and EPIC hospital clinical digital journal system hosted in the Capital Region of Denmark. REDCap is a secure web-based data collection application. To limit typos the applications is coded to independently audit the data and warn the investigator immediately in case of double data entry, values beyond normal ranges and/ or missing data values. During data entry, the application will remind the assessor to cross-check that the questionaries for the visit are completed and that the next visit is planned. If data for each patient is not entered in Redcap within 3 days of the expected visits, the application will send a reminder by mail to the primary investigator thus minimizing missing values in the dataset. Identifying information about the patients will be stored in secured hospital servers. The primary investigator will have access to the trial data and final dataset. The study is approved and monitored by the Danish Data Protection Agency (Pactius) and it will follow the General Data Protection Regulation and Data Protection Act. The anonymized results will be made available for meta-analysis and systematic reviews.

## Discussion

Today, operative treatment for scaphoid delayed union or non-union is performed with the conventional open technique or the arthroscopic technique based on the preference of the surgeon. Based on non-randomized studies both techniques appear safe and with no major differences in functional outcome or adverse events [16, 35]. There is, however, disagreement regarding the treatment of patients with a large deformity. Hegazy et al. [36] and Sayegh and Strauch [13] found superior correction and superior ROM, Q-DASH and Mayo wrist scores in patients treated with a structural graft compared with patients treated with a non-structural graft. Other studies found no difference in deformity correction [15, 37, 38].

The arthroscopic technique is potentially less invasive with minimal donor site morbidity and potentially faster time to union [15] because of minimal trauma to the ligament structures, joint capsule and the tenuous blood supply [19]. It may also have advantageous osteogenic properties compared to a structural graft [39]. Differences in time to union between the open technique and the arthroscopic technique have, to our knowledge, never been investigated.

X-ray is commonly applied to monitor union after operative treatment for scaphoid delayed/non-union. Consolidation on at least three out of four views is a sign of union [40]. X-ray is not reliable to determine fracture displacement and deformity [41], and the wrong position of the hand and “overlining” in the fracture line can complicate the evaluation of union. CT scans are reportedly more accurate and reliable in the assessment of union [26, 42–44]. We aim to provide a more accurate measurement of time to union with repeated CT scans.

The study differentiates from standard treatment with up to 7 scheduled CT scans in patients with prolonged union time, compared to 1–3 CT scans and 1–3 X-rays as a standard follow-up. The background radiation in Denmark is 3 mSv each year. Each CT scan is performed with the involved wrist above the head with a mean radiation dose of 0.03 mSv. The wrist contains minimal radiation-sensitive red bone marrow and the cumulative radiation dose is maximal 0.21 mSv, (category IIA, international commission on radiation Protection), corresponding to 21 days of background radiation [45]. The radiation dose of each scaphoid X-ray is 0.0002 mSv.

We aim to decrease observer and selection bias through blinding and randomization, stratified for tobacco-smoking habits, fracture displacement (> / < 2 mm) and proximal pole fractures. By adding 20% to the sample size, we compensate for dropouts and attempt to avoid Type-II errors. Potential dropouts will be minimized with permission to contact patients by mail or phone if they do not show up for follow up-visit or if data is missing.

The patients will not be blinded to their treatment allocation. Sham surgery can be used to blind patients regarding skin incisions and subsequently the surgical technique. However, all patients treated with open bone grafting using a cancellous graft taken from the iliac crest will be operated on in general anaesthesia, while arthroscopically treated patients undergoing the treatment in regional block anaesthesia. Furthermore, the use of graft from the iliac crest in one group and not the other makes it difficult to blind patients as donor-side pain is expected. Finally, we do not expect patients to have an expectation of open- or arthroscopic-assisted graft reconstruction to be superior to the other.

Observer bias is minimized with a blinded musculoskeletal radiologist for the primary outcome, to prevent observer bias from favouring one of the interventions.

The secondary outcome (Q-DASH) is reported by the patient independently, thus with no implication to the assessor. Other secondary outcomes are evaluated by an independent, non-blinded observer.

The current standard treatment at our department includes follow-up until the union is established. In this study, we will have additional follow-up examinations at 6 months and at 1 and 2 years. It has the risk of keeping the patients in the role of being ill. However, the patients can have a feeling of extra good care with the possibility to address uncertainty or problems more easily.

Patients are at risk of being treated inferior with an intervention which is deemed inferior with the study analysis, but nothing a priori suggests which intervention is the better one.

The trial will provide high-quality evidence regarding time to union and short- and long-term functional outcomes of open and arthroscopic assisted graft reconstruction for scaphoid delayed/non-union.

The results from the study can contribute to establish a treatment algorithm for scaphoid delayed/non-union together with results from other studies.

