## Method and analyses

### Study design

This is a single-centre, 1:1 observer-blinded randomized controlled, superiority trial. The main objective is to compare open C graft with arthroscopic assisted C chips graft reconstruction for scaphoid fractures with delayed/non-union.

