## Blinding

In this observer-blinded RCT, union is assessed by a blinded musculoskeletal radiologist. QDASH is a patient-reported survey, without the involvement of surgeons or research staff. Other secondary outcomes will be measured by an independent observer. The study will not be blinded to the operating theatre staff, surgeons, physiotherapists or patients.

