#### Secondary outcomes

For *radiographic outcomes*, the union rate will be evaluated with CT scans undertaken every second week. DCA and HLR will be measured preoperative and at follow-up on CT scans to evaluate the correction of deformity [11, 31].

*Pain* at rest and activity is recorded on a visual analogue scale (VAS), ranging from 0 to 10, with 10 reflecting the worst and 0 representing no pain in the wrist.

*Donor site morbidity* located to the iliac crest (Group O) and distal radius (Group A) are evaluated with VAS ranging from 0 to 10, with 10 reflecting the worst and 0 representing no pain in the wrist.

*Range of motion* (ROM) is measured in degrees with a goniometer and recorded in arcs for flexion/extension, supination/pronation and radial/ulnar deviation, compared to the unaffected wrist.

*Grip strength* is measured in kilograms with a Jamar dynamometer with the elbow will be in 90° flexion and attached to the chest compared to the unaffected [32].

*Key pinch* is measured in kilograms using a pinch gauge with the elbow in 90° flexion and attached to the chest, compared to the unaffected wrist [33].

*Patient satisfaction* is evaluated with the following question: What is the function of your hand today, compared to before surgery? With the following answer options: (1) disaster, (2) much worse, (3) slightly worse, (4) unchanged, (5) slightly better, (6) much better, (7) recovered. Second, for future research perspective, patients are asked: when you consider the following parameters: the activities you can carry out in daily life, your pain, your function of the hand, do you think your current situation is satisfactory? (yes/no) [34].

*EQ5D-5L* will be used to estimate the threshold for acceptable cost-utility ratio — the threshold for how much healthcare providers will pay for an extra quality-adjusted life year (QALY). The cost-utility of the arthroscopic and open techniques will be compared. Baseline and 2-year follow-up scores will be compared. A cost model will be defined from patient data, clinical records, and unit costs from the Danish healthcare system. Length of hospital stay, discharge, pain medication usage and readmission will be recorded.

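### The trial is labelled observer-blinded, but the Discussion says the observer of the other secondary outcomes, which include range of motion, grip and key pinch, is not blinded

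*Protocol article*

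**What the plan says.** The abstract's Methods paragraph and the Study design section both label the trial observer-blinded; the latter reads "This is a single-centre, 1:1 observer-blinded randomized controlled, superiority trial".

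The Blinding section ties the label to the primary outcome: "In this observer-blinded RCT, union is assessed by a blinded musculoskeletal radiologist". On the rest it says "QDASH is a patient-reported survey, without the involvement of surgeons or research staff" and "Other secondary outcomes will be measured by an independent observer". It closes with the unblinded parties: "The study will not be blinded to the operating theatre staff, surgeons, physiotherapists or patients".

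The Discussion sets an aim, "We aim to decrease observer and selection bias through blinding and randomization", and repeats that a blinded radiologist protects the primary outcome. It then adds "Other secondary outcomes are evaluated by an independent, non-blinded observer".

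On deformity, the Secondary outcomes section says "DCA and HLR will be measured preoperative and at follow-up on CT scans to evaluate the correction of deformity". It does not say who takes these measurements.

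**The concern.** Someone who reads only the Blinding section would reasonably take the independent observer to be blinded. The trial carries that label, and the observer is not on the list of people who are unblinded. The Discussion says the opposite of the same observer. Both statements are current text.

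This matters for measurements that depend on the examiner. Goniometer readings, and strength tests that vary with coaching and effort, can drift when the examiner knows the operation. The patient knows it too, so neither party to these tests is masked. The Discussion promises high-quality evidence on short- and long-term function. It also presents motion and deformity correction as matters on which earlier studies disagree, so readers will look at these comparisons.

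**Working it through.** No figure in the article bears on this point, so the check is mainly a comparison of its statements.

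**1. The observer's status, section by section**

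| Section | What it says of the observer |
|---|---|
| Abstract, Study design | Trial is observer-blinded; no detail |
| Blinding | Independent; blinding not stated; absent from the list of unblinded roles |
| Discussion | Independent and not blinded |

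Independence and blinding are different properties, so the Blinding section does not literally contradict the Discussion. It leaves out what the Discussion discloses, under a label that suggests otherwise.

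**2. Is a reason given?** The Discussion cites the type of anaesthesia, expected donor-site pain and patients' lack of prior preference. All three concern the blinding of patients. None explains why an assessor must know the arm.

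**3. Which outcomes are affected?** Leaving out Q-DASH, the abstract lists 11 secondary outcomes:

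- Patient-reported by unblinded patients, so masking an observer changes nothing: pain VAS, donor-site VAS, EQ5D-5L, satisfaction (4).
- Resting on the CT union reading already given to the blinded radiologist: union rate (1).
- Drawn from questions to patients and journal notes (Adverse events section), and likely to reveal the operation: complications, revision surgery (2).
- Measured by an examiner: range of motion, grip, key pinch (3).
- Measured on CT, reader not named: deformity by DCA and HLR (1).

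The total is 4 + 1 + 2 + 3 + 1 = 11. The last two groups, 3 + 1 = 4 outcomes, are those that could be newly blinded using roles the article already describes. With union rate that makes 5 of 11, or 5 of the 11 − 4 = 7 that are not patient-reported.

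**4. What a bias could do (illustration only).** Assume that knowing the arm shifts a measure by d standard deviations in one direction when there is no true difference. Take n = 36 per group from the Sample size calculation section and a two-sided 5% test. The noncentrality is d × √(n/2) = d × √18 = d × 4.243, and the false-positive rate is P(|Z + noncentrality| > 1.96).

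| Assumed d | Noncentrality | False-positive rate |
|---|---|---|
| 0 | 0 | 5.0% |
| 0.1 | 0.42 | 7.1% |
| 0.2 | 0.85 | 13.6% |
| 0.3 | 1.27 | 24.7% |

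The values of d are assumptions; the article gives no basis for any of them.

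**The case against.** The strongest reply is that this is a disclosed choice. The Blinding section links the label to the radiologist's reading of union and never says the other observer is blinded, and the Discussion states openly that this observer is not. The primary outcome is protected, and the designated primary functional outcome, Q-DASH, involves no assessor. This stands as a limit on importance. It does not explain why the section devoted to blinding omits the fact, or why the observer is unblinded at all.

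A reader might infer four stronger things that the document does not support:

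- **That most secondary outcomes could be blinded without extra staff.** Only 4 of 11 could be newly blinded, and the article says nothing about staffing. If one person both tests the wrist and asks about donor-site pain (iliac crest in one group, distal radius in the other) or complications, those questions can unmask that person. The article does not say who asks them.
- **That DCA and HLR are read unblinded.** They sit in the same paragraph as the CT union rate, with no reader named. Taking the Discussion's phrase literally would also hand union rate to the unblinded observer, which conflicts with the radiologist's role. The reader is unstated, not shown to be unblinded.
- **That the error rates above describe this trial.** They also require a bias that consistently favours one arm. The Discussion says nothing beforehand points to the better operation, although the stated hypothesis favours arthroscopy.
- **That the primary result is in doubt.** Nothing on this point touches it.

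**Conclusion.** The concern holds in a limited form. A trial labelled observer-blinded has, by its own Discussion, a non-blinded observer for its other secondary outcomes. The Blinding section does not say so, and no reason is given. Range of motion, grip and key pinch are exposed to detection bias. DCA and HLR are exposed only on a literal reading of the Discussion and otherwise simply lack a named reader. The primary outcome, Q-DASH and the other patient-reported outcomes are not affected.

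The size of any bias cannot be derived from the document. The conclusion rests on two assumptions: that the Discussion describes what will actually be done, and that these tests are sensitive to an examiner's knowledge of the arm. It is a low-severity point: a wording defect together with an inexpensive missed protection.

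**What to change.** 1. **Deformity.** State that the blinded radiologist measures DCA and HLR on the CTs already being read. Cost: a few minutes of measurement per scan used.
2. **Motion and strength.** Keep the existing independent observer unaware of allocation for range of motion, grip and key pinch. Cover the incisions (for example with a thin opaque sleeve) and ask patients not to disclose their operation. Collect donor-site pain and complications after these tests or by questionnaire, so that the answers cannot unmask the observer beforehand.
3. **Wording.** Make the Blinding section and the Discussion agree on this observer's status, and limit the observer-blinded label to the outcomes for which it holds. If step 2 is judged unworkable, add the observer to the list of unblinded roles and give the reason. This step costs only an edit.

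The downside is that masking may be imperfect, since patients may still disclose their operation, and goniometry over a covering is slightly less convenient. Sample size, treatment and visit schedule do not change.

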### Trial status

Version 2.0, February 3, 2023.

Start of inclusion: February 15, 2023.

Finish date of recruitment: February 15, 2026

## Data Availability

The electronic data will be stored in closed drivers and on REDCap. Printed data will be stored in closed cabinets. The deidentified dataset and results will be available from the primary investigator on request.

## Abbreviations

RCT: Randomized controlled trial
CC: Corticocancellous
C: Cancellous
C-chips: Cancellous chips
CT: Computed tomography
AVN: Avascular necrosis
Q-DASH: Quick Disability of the Shoulder and Hand
VAS: Visual analogue scale
QALY: Quality-adjusted life year
ROM: Range of motion
MRI: Magnetic resonance imaging
SNAC: Scaphoid non-union advanced collapse
DISI: Dorsal intercalated segment instability
DSA: Dorsal cortical angle
HLR: Height-length ratio
MCR: Mid-carpal radial
MCU: Mid-carpal ulnar
FCR: Flexor carpi radialis
MCID: Minimal Clinical Important Difference
SD: Standard deviation
IQR: Interquartile range
REDCap: Research Electronic Data Capture
